### 2.8. Study Procedures

Prior to participating in the study, nurses will be briefed about the project and provided with a brief education about using the PCI. This will ensure that each nurse receives the same information. No further instruction will be provided on the PCI which will remove the risk of researcher influence.

Each nurse will be allocated a code that will be used for each assessment they complete. This code will not identify the nurse and will be provided by an independent person, it will be used for analysis purposes only. The code will be allocated to each nurse involved using a sealed envelope system at the commencement of the project and on consent. This will ensure that data related to the learning effect can be analyzed.

The nurses will be provided with an introduction to the PCI and asked to complete the nurse pre RCT survey (File S1 in Supplementary). On completion of data collection, the nurse will be asked to complete the post RCT survey (File S2 in Supplementary).

As described earlier in local context, the Intake Nurse is responsible for allocating new referrals for assessment to nurses through a daily list. They will in addition provide the sealed group allocation envelope to the nurse on return to the office. On return, the nurse will open the envelope to determine the group type. The nurse will then retrieve the appropriate group envelope containing the required study documents. The control group envelope will contain the nurse information and consent (File S3 in Supplementary) and the nurse assessment survey 1 (File S4 in Supplementary). The intervention group envelope will include, in addition to the above, the PCI (File S5 in Supplementary) and the nurse assessment survey 2 (File S6 in Supplementary).

The control group: an assessment will be completed following the current usual process. The nurse conducting the assessment will be asked to rate and justify the client’s complexity using judgment as usual and will not be prompted in any way.

The intervention group: an assessment, documentation and data collection will be carried out as for the control group with exception of the inclusion of survey 2. Once client assessment has been completed and away from client interaction, the nurse then completes the PCI and nurse survey 2 which comprises of questions pertaining to the PCI. The researcher will not lead or prompt the nurses.

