### 2.9. Outcomes

The primary outcome of the RCT component is client complexity rating (low, moderate, or high) as measured using the PCI (intervention) or usual assessment nurse judgment alone (control).

The first secondary outcome is the addition of nursing care interventions after initial assessment. These are the required interventions for the client based on the assessment outcome and the detected level of client complexity. The nursing care interventions will be categorized as medication support, wound care, referrals and liaison and others. The second secondary outcome is the nursing care time added in minutes. This is the additional time that may be allocated to the delivery of the nursing care interventions for the clients following assessment and detected level of client complexity. 

Data will be collected using baseline and follow up surveys (File S1 and S2 in Supplementary) completed by participating nurses allocated to the intervention group pre- and post-PCI use. The survey will be administered electronically or via paper form. It will be supplemented with field notes and observations recorded by the researcher throughout the study. Any focus groups or interviews conducted will be recorded for transcription.

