### 2.10. Data Analysis

Statistical analysis will be carried out in IBM SPSS Statistics Version 24 (IBM Corp, New York, NY, USA). For quantitative data analysis, statistical significance will be indicated by *p* < 0.05.

Participant characteristics and survey data will be analyzed and presented using summary descriptive statistics. Statistics will include mean and standard deviation for continuous data, median and interquartile range for ordinal data and percentage and 95% confidence interval for nominal data. Comparative univariate statistics will be conducted to test for differences between control and intervention characteristics. Parametric and or non-parametric statistical tests will be used to compare the groups.

Currently the PCI has no cut-offs for the level of complexity ratings. Preliminary data will be used in a receiver operating characteristics (ROC) analysis to determine complexity rating cut-offs (categorized as low, moderate, or high) with usual care complexity rating as the criterion. Categorial level of complexity rating as a primary outcome will be compared between control and intervention groups using the Chi-square independence test.

For the first secondary outcome, modification of nursing interventions (addition or subtraction of nursing interventions), between group comparisons will be performed on distribution of intervention categories. The second secondary outcome, clinical time will be compared between the study groups using ordinal regression. Clinical time as the dependent three level categorical variable. Age and nurse’ years of community experience will be covariates, while gender, reason for referral, group allocation (intervention or control) and level of complexity rating will be factors in the regression analysis.

Qualitative data collection will be from surveys, additional information regarding nursing interventions, nurse’s feedback, field notes and observations recorded by the researcher. Audio-recorded information from focus groups will be transcribed verbatim. Inductive thematic analysis has been chosen because this will ensure that themes emerge from the data (bottom-up approach). Analysis will be conducted using Braun and Clarke’s phases which include (1) data familiarization, (2) initial code generation, (3) theme search, (4) review of themes, (5) define and name themes [46].

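### Section 2.8 appears to have the nurse record the usual-judgment complexity rating after learning the arm, although that rating needs no allocation and could be locked first

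*Protocol article*

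**What the plan says.** Section 2.8 of the Protocol article gives the order of events. The Intake Nurse hands over the sealed allocation envelope when the assessing nurse is back at the office. Then: "On return, the nurse will open the envelope to determine the group type". The study forms come next: "The nurse will then retrieve the appropriate group envelope containing the required study documents".

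The contents of the two packs are listed. "The control group envelope will contain the nurse information and consent (File S3 in Supplementary) and the nurse assessment survey 1". "The intervention group envelope will include, in addition to the above, the PCI", together with survey 2.

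On the rating itself, the control-arm text says: "The nurse conducting the assessment will be asked to rate and justify the" client's complexity by usual judgment, without prompting. For the intervention arm, "data collection will be carried out as for the control group with exception of the inclusion of survey 2". The PCI and survey 2 follow once the client assessment is finished.

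The rating is then used in two places. Section 2.9 defines the primary outcome as a low, moderate or high rating "as measured using the PCI (intervention) or usual assessment nurse judgment alone (control"). Section 2.10 says that the PCI has no cut-offs yet and that a ROC analysis of preliminary data will set them, "with usual care complexity rating as the criterion".

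**The concern.** Rating a client's complexity by ordinary clinical judgment is the same task in both arms. The nurse does not need to know the allocation to do it. Even so, the order in 2.8 puts the reveal first and the form second.

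Two uses of the rating are exposed, and they fall on different clients.

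- **Control arm.** The rating is the primary outcome. Section 2.10 compares it by chi-square with categories derived from the PCI. The rater has been educated in the PCI and knows that this client is in the comparator arm. Section 2.2 itself describes the interpretation of assessment information as largely subjective.
- **Intervention arm.** A ROC analysis needs a PCI score and a judgment rating on the same client, and only intervention clients have a PCI score. If the preliminary data are trial data, the criterion is therefore a rating made by a nurse who knows that the PCI follows and has the form in the same pack. The criterion is then not protected from the instrument that it calibrates, and the resulting cut-offs define the intervention-arm primary outcome.

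No later analysis can recover an arm-blind rating that was never taken.

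**Working it through.** **1. Order of events, set side by side**

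| Step | Control | Intervention | Source |
|---|---|---|---|
| Return to office, receive sealed envelope | yes | yes | 2.8 |
| Open envelope, arm known | yes | yes | 2.8 |
| Retrieve pack for that arm | information and consent, survey 1 | the same, plus PCI and survey 2 | 2.8 |
| Usual-judgment rating recorded | survey 1 (inferred) | survey 1 (inferred) | 2.8 |
| PCI scored | no | yes, after the assessment | 2.8 |

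Apart from the information and consent papers, survey 1 is the only form listed in the control pack. The rating therefore has no other listed place. This is an inference, because File S4 is not shown.

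Section 2.7 has an envelope drawn and opened whenever an assessment is due. That reads as a reveal before the assessment, so it puts the reveal no later than 2.8 does. On either reading the form is reached after the arm is known.

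**2. Number of ratings exposed**

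Section 2.7 gives 45 blocks of 4: 45 × 4 = 180 allocations, which matches the target of 180 (90 per group) in 2.6. If survey 1 carries the rating, up to 90 control-arm outcomes and up to 90 intervention-arm criterion ratings are recorded after the reveal.

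**3. Effect on control ratings**

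The documents give no size and no direction, so no figure is offered.

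**4. Effect on the ROC criterion (illustration only)**

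Assumptions:
- PCI score and judgment are bivariate normal with correlation r.
- A high rating is the top 23.1% on judgment (the control-arm proportion in 2.6).
- A share f of criterion ratings is replaced by the PCI's own top 23.1%.

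Both r and f are assumed; neither comes from the documents. With 2,000,000 simulated clients, the AUC for a high rating is:

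| r | f = 0% | 10% | 20% | 30% |
|---|---|---|---|---|
| 0.3 | 0.646 | 0.681 | 0.716 | 0.752 |
| 0.5 | 0.744 | 0.769 | 0.795 | 0.820 |
| 0.7 | 0.845 | 0.860 | 0.876 | 0.891 |

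Check by hand: the proportion rated high stays at 23.1%, so the AUC is linear in f, AUC(f) = AUC(0) + f × (1 − AUC(0)). For r = 0.3 and f = 30%: 0.646 + 0.3 × 0.354 = 0.752. For r = 0.5 and f = 10%: 0.744 + 0.1 × 0.256 = 0.770. The table agrees to within 0.001.

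**5. What locking the rating would not remove**

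Now keep the rating fixed before the reveal, and set a share f of PCI scores to the nurse's own judgment instead. At f = 10%, 20% and 30% the AUC is 0.681, 0.717 and 0.752 (r = 0.3); 0.769, 0.795 and 0.820 (r = 0.5); 0.860, 0.876 and 0.891 (r = 0.7). The inflation is practically the same. Locking the rating closes influence from the PCI on the rating, but not from the rating on the PCI.

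**The case against.** The case on the other side has real content.

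- **The place of the rating is inferred.** Section 2.8 has the control assessment follow the usual process, and 2.2 describes the complexity judgment as part of that process. The judgment may be formed, and perhaps written down, at the visit. A condensed article may also leave the order of forms to its supplements. This stands as a limit on certainty. It does not remove the point, because 2.8 fixes the order of reveal and forms, and no sentence requires the rating to be recorded first.
- **There are protections already.** Under 2.8 the reveal comes after the visit, the PCI follows the assessment, and nurses are not prompted or led. These shield the visit and limit the researcher's influence. They do not blind the recorded rating or require it to be finished before the PCI is seen.
- **Nurses cannot be blinded.** This is true for completing the PCI, but not for a rating that both arms give in the same way.
- **The illustration is strained.** The PCI has no cut-offs, so a nurse cannot match an exact percentile of it. The ROC is meant to set cut-offs, whereas the table shows AUC. Only looser influence is plausible. This stands.
- **The remedy is partial, and consent sits in the same pack.** Both are right, and the fix allows for them.
- **It is a pilot.** Section 2.6 says so, which lowers the stakes. The same section, however, projects a definitive trial from these complexity ratings.

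A reader might infer that the control-arm outcome is biased in a known direction, or that the PCI's accuracy will be inflated by the amounts in the table. The documents support neither. Nor do they show that the PCI is scored before the rating is made; 2.8 implies the reverse order without enforcing it.

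**Conclusion.** The concern holds in a limited form. As 2.8 is written, a subjective rating appears to be recorded with the arm known and, in the intervention arm, with the PCI in the same pack. That rating is the control-arm primary outcome and, if the preliminary data are trial data, the ROC criterion. The design does not need this exposure.

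The conclusion rests on two assumptions: that survey 1 carries the rating, and, for the ROC part, that the preliminary data come from the trial. Up to 180 ratings are affected. The effect on control ratings is unknown in size and direction. For the ROC criterion, the assumed alignment of 10% to 30% raises the AUC by about 0.015 to 0.106 over the correlations tried (0.860 − 0.845 and 0.752 − 0.646); an alignment of 0% raises it by nothing. The case for change is that a simple reordering removes an avoidable source of bias, not that bias has been shown.

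**What to change.** Take the usual-judgment rating and its justification out of both group packs and hand them over with the sealed allocation envelope. Move the nurse information and consent with them, unless consent has already been given at commencement, so that no rating is made before consent. Any survey 1 items on care interventions or time can stay in the packs, so that an effect of the PCI on them is still captured.

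State in 2.8, for example: *After the client visit the nurse completes and signs the usual-judgment rating, which is not changed afterwards, and only then opens the allocation envelope.* Align 2.7 with this order. Name this locked rating as the control-arm outcome in 2.9 and as the ROC criterion in 2.10.

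The cost is one more form at hand-over (plus the consent papers where needed) and short edits to these sections. No extra clients or analyses are needed, and the PCI comparison is unchanged.

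Two limits remain and should be stated. PCI education is shared by both arms, so judgment ratings may already be coloured by it. The same nurse scores the PCI after rating, so PCI scores may still be drawn towards that nurse's own rating.

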### 2.9. Outcomes

The primary outcome of the RCT component is client complexity rating (low, moderate, or high) as measured using the PCI (intervention) or usual assessment nurse judgment alone (control).

The first secondary outcome is the addition of nursing care interventions after initial assessment. These are the required interventions for the client based on the assessment outcome and the detected level of client complexity. The nursing care interventions will be categorized as medication support, wound care, referrals and liaison and others. The second secondary outcome is the nursing care time added in minutes. This is the additional time that may be allocated to the delivery of the nursing care interventions for the clients following assessment and detected level of client complexity. 

Data will be collected using baseline and follow up surveys (File S1 and S2 in Supplementary) completed by participating nurses allocated to the intervention group pre- and post-PCI use. The survey will be administered electronically or via paper form. It will be supplemented with field notes and observations recorded by the researcher throughout the study. Any focus groups or interviews conducted will be recorded for transcription.

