### 1.5. Aim and Objectives

The Improving Detection of Patient Complexity in the Community (ImPaCt) is a trial of the PCI within the community nursing service to improve detection of client complexity in regional Victoria. The primary objective is to explore whether adding the PCI to the usual assessment process could enhance the detection of the complexity of clients and support the clinical judgment. The secondary objective is to explore whether using the PCI derived client complexity could facilitate appropriate resource allocation; these resources being the time allocated to providing clinical care to the complex client or referrals completed to support the client. The study will also explore issues around the feasibility and acceptability of the PCI in community nursing.

This study aims to answer the question “Does the PCI in addition to usual assessment, enhance nurses’ detection of complexity and delivery of appropriate allocation of care for community dwelling patients aged 65 and over?”.

The primary null hypothesis is the addition of the PCI has no effect on nurses’ detection of patient complexity compared to usual assessment alone. The secondary null hypothesis is the addition of the PCI does not enhance the allocation of appropriate resources according to the client’s complexity. 

Ethical approval has been provided by the researchers’ employer and the supporting University reference number (blinded). The trial has been registered with the Australian and New Zealand Clinical Trials Registry (blinded).

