### 2.6. Sample Size

Initial data will be used to conduct a post hoc sample size calculation. Up to *n* = 34 (all) nurses in the community nursing service will make up the nurse participant sample. These are nurses making up the team who would normally be available to conduct assessments on referred clients. Based on the number of new referrals expected over three-month period, a convenience sample of up to *n* = 180 patient assessments (90 per group) will be targeted and up to *n* = 27 (all) nurses in the service will make up the nurse participant sample. Due to the pilot nature of the study, formal sample size calculation is not critical. Pilot studies by their nature are not aimed at establishing a definitive effect, however a rationale for sample size basis such as described above is deemed sufficient [44,45].

Using our early pilot data, post hoc sample size calculation was performed based on the proportions of the level of complexity rating in the ImPaCt study. A minimum total sample *n* = 138 patient assessments, i.e., 69 per group (Figure 1) will be required in definitive trial to detect a significant difference in proportions relating to a high level of complexity rating between the control (23.1%) vs. intervention (5.7%), odds ratio = 4.97, power = 0.8 and *p* < 0.05.

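### The primary outcome is the PCI category in one arm and the nurse's judgment in the other, so a difference in ratings cannot be read as better detection by nurses

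*Protocol article*

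**What the plan says.** Section 1.5 sets the objective as exploring whether "adding the PCI to the usual assessment process could enhance the detection of the complexity of clients and support the clinical judgment". It asks "Does the PCI in addition to usual assessment, enhance nurses’ detection of complexity and delivery of appropriate allocation of care", and states: "The primary null hypothesis is the addition of the PCI has no effect on nurses’ detection of patient complexity compared to usual assessment alone". All three concern the nurse's detection when the tool is added to usual practice.

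Section 2.9 defines the primary outcome as "client complexity rating (low, moderate, or high) as measured using the PCI (intervention) or usual assessment nurse judgment alone (control"). Section 2.10 explains how a PCI score becomes such a rating. It notes that "Currently the PCI has no cut-offs for the level of complexity ratings", and plans to derive low, moderate and high bands by ROC analysis of preliminary data "with usual care complexity rating as the criterion". The resulting categories are compared between arms by a chi-square test of independence.

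Section 2.8 says that in the intervention arm "an assessment, documentation and data collection will be carried out as for the control group with exception of the inclusion of survey 2". The nurse fills in the PCI and survey 2 after the client assessment is finished and away from the client. Section 2.6 sizes a definitive trial on the share rated high, "between the control (23.1%) vs. intervention (5.7%), odds ratio = 4.97".

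**The concern.** The intervention is also the measuring instrument, and only in one arm. Randomisation makes the expected true complexity of the clients equal between arms, but it does not make two different instruments comparable. If the PCI bands sit higher or lower than nurses' own sense of 'high', the arms will differ even when no nurse changes a judgment. If the bands give the same shares as nurse judgment, the arms will agree even if individual clients are reclassified correctly in both directions.

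Nothing in the plan says which direction would be an improvement, and no reference rating outside the two methods is named. A significant result could then be reported as enhanced detection, and a definitive trial built on the same contrast, when the data show only that two ways of rating give different distributions.

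**Working it through.** **1. Is the intervention-arm outcome the PCI category or the nurse's rating?** Section 2.9 says the rating is measured with the PCI. Section 2.10 agrees: cut-offs are needed only if the PCI score itself is turned into the category. Sections 2.1 and 2.5 describe the intervention as the PCI plus usual assessment, which would fit a combined nurse rating, but no section makes such a rating the outcome. Because the PCI is completed after the assessment (section 2.8), it can alter a nurse's detection only through a judgment made after it. The article describes no such judgment.

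**2. Does anchoring the cut-offs to usual care solve it?** Let π be the share that usual care rates high, and Se and Sp the sensitivity and specificity of the PCI cut-off against that rating. The PCI then labels as high a share of

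Se·π + (1 − Sp)·(1 − π).

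This equals π only if (1 − Se)·π = (1 − Sp)·(1 − π), that is, if misses and false positives cancel. An ROC cut-off does not guarantee that. Where they do cancel, the chi-square test is pulled towards no difference by construction. In either case the control method serves as the standard for the tool that is meant to improve on it.

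**3. The plan's own figures.** Inputs from section 2.6: 23.1% (control), 5.7% (intervention), power 0.8, p < 0.05 (two-sided assumed), 69 per group, target up to 90 per group.

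- Odds ratio = (0.231/0.769)/(0.057/0.943) = 4.97, as stated.
- Sample size: the two-sided Fisher exact test has power 79.5% at 68 and 80.2% at 69 per group, so 69 per group (138 in total) reproduces. The uncorrected chi-square formula gives 63 per group. The sample size is not at issue here.

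**4. Illustration: no change in nurses' judgment.** Assume nurses would rate 23.1% high in both arms, while the PCI cut-off labels a share q as high. The rejection probability of the two-sided two-proportion test, normal approximation, is Φ[(d − 1.96·se0)/se1] plus a negligible opposite tail when d is large, where

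- d = 0.231 − q
- se0 = √[2·p̄(1 − p̄)/n], with p̄ = (0.231 + q)/2
- se1 = √{[0.231·0.769 + q(1 − q)]/n}

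For q = 0.057 and n = 69: d = 0.174, p̄ = 0.144, se0 = 0.0598, se1 = 0.0579. Then (0.174 − 0.1172)/0.0579 = 0.98, and Φ = 0.837.

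For q = 0.057 and n = 90: se0 = 0.0523, se1 = 0.0507. Then (0.174 − 0.1026)/0.0507 = 1.41, and Φ = 0.921.

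| Share the PCI cut-off labels high | Rejection, 69 per group | Rejection, 90 per group |
|---|---|---|
| 23.1% | 5.0% | 5.0% |
| 20% | 7.3% | 8.0% |
| 15% | 22.7% | 28.2% |
| 10% | 54.5% | 66.0% |
| 5.7% | 83.7% | 92.1% |

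The table uses high against not high and independent assessments. The planned test uses all three levels.

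**The case against.** The strongest case on the other side is that this is a pragmatic pilot comparing two assessment strategies. The objective is exploratory, the null hypothesis is non-directional, and section 2.6 says pilots do not aim at a definitive effect. Nurses score the PCI items themselves, so the PCI is a structured form of nurse judgment. The cut-offs are tied to usual care ratings rather than freely chosen. Surveys 1 and 2 are supplementary files not shown here, so a nurse rating after the PCI may be collected.

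Part of this stands. The design can support a statement that the two methods give different distributions of ratings. An unseen survey item may exist, but section 2.9 does not make it the outcome. Pilot status does not remove the problem, because the plan tests at p < 0.05 and sizes the definitive trial on the same contrast.

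The documents do not support several stronger readings that a reader might infer:

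- *That the early data show the PCI finding about four times fewer high-complexity clients (23.1/5.7 = 4.05).* Section 2.6 labels the figures only by arm. That 5.7% is a PCI category is an inference from section 2.9. Even on that inference, the figures could mean over-rating by nurses or missed cases by the PCI.
- *That the gap equals a definite shift on the 6 to 30 scale.* The article gives no distribution or standard deviation of PCI scores.
- *That the trial can answer nothing.* Added interventions and added nursing time are defined alike in both arms and remain comparable.
- *That better tracking of added time or interventions would prove enhancement.* Section 2.9 makes both follow from the detected level of complexity, so they are not an independent standard.

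**Conclusion.** The point holds as a mismatch between the measurement and the claim. Sections 2.9 and 2.10 compare PCI categories with nurse judgments, while section 1.5 asks about nurses' detection. Nothing else in the article reconciles them. A significant chi-square would show that the ratings differ. It would not show that nurses detect complexity better, and a non-significant one would not exclude that they do. This must be corrected before any claim of enhanced detection is made.

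The 84% and 92% rejection probabilities are an illustration of what a difference in cut-off alone could produce, not an estimate of bias in this trial. They assume nurse judgment unchanged at 23.1% high, a PCI cut-off that labels 5.7% high, independent assessments and a two-sided 5% test. The argument itself does not depend on them.

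**What to change.** - **Primary outcome (section 2.9).** Use the nurse's own low/moderate/high rating, on the same item in both arms: after the PCI in the intervention arm, after usual assessment in the control arm. Add no extra prompt in the control arm, since section 2.8 rules out prompting there. Reconcile sections 2.1, 2.5 and 2.9 with this definition.
- **No adjustment for a first rating.** Under section 2.8 the nurse opens the allocation before retrieving the survey, so any earlier rating would be made with the arm known and is not a clean baseline covariate.
- **PCI score.** Keep it as a process measure. Section 2.8 implies that the intervention arm has both a judgment rating and a PCI score for the same client. Report their paired agreement by weighted kappa and a test of marginal homogeneity.
- **Claim.** Limit the primary conclusion to whether the PCI changed the ratings. Do not conclude that detection was enhanced, because the plan has no independent reference standard.
- **If data collection has ended.** Section 2.2 dates participation from July 2019 to September 2020, and section 4 refers to an inquiry concluded in 2021, so this is possible. In that case apply the paired analysis and the narrower claim now, and introduce the common rating item in the definitive trial that section 2.6 sizes.

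The cost is one item on the nurse form, revised outcome and analysis wording, and a weaker headline claim.
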